## Objectives

We are conducting a multicenter, randomized, controlled, double-blind, double-dummy clinical trial to compare the effectiveness of two Chinese patent medicines for angina patients diagnosed with qi deficiency and blood stasis syndrome. The ultimate goal is to test the proposed methodology for the individualized evaluation of the therapeutic effects of Chinese patent drugs and for distinguishing between drugs targeting a multitude of similar indications.

To fulfill these objectives in our present study, we highlight the introduction of trial participants’ therapeutic needs and willingness in terms of group allocation and the use of CER methodology. Specifically before being entered into the randomization process, all eligible participants with qi deficiency and blood stasis syndrome will first be allowed to choose from among four prespecified groups of symptoms which they would most like to be addressed. The outcomes for these symptoms are considered PIOs and will be assessed using PRO instruments. Furthermore, we will test the use of the CER method to compare the curative effects of QSYQ dripping pills and TXL capsules, two widely used Chinese patent medicines for angina patients with qi deficiency and blood stasis syndrome. By analyzing and comparing the effects of the two drugs for each symptom group, we aim to summarize the characteristics of the drugs’ curative effects and identify the best targeted indications for each drug.

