### Patient grouping and treatment allocation

Using stratified and blocked randomization, we will first categorize eligible participants into four groups on the basis of their varied choice of secondary symptoms to be addressed, and then we will randomly assign them to one of the two treatment arms at a ratio of 1:1. To minimize imbalances across groups, gender will also be used as a stratification factor. The random number sequence will be generated by a third-party statistician using SAS version 9.1 software (SAS Institute, Cary, NC, USA).

The four symptom combination groups, each representing the signs a patient most wishes to bring under control, were formed according to the characteristic physical manifestations of the qi deficiency and blood stasis syndrome defined in the 2002 Guidelines for Clinical Research of Chinese Medicine (new drug). The grouping criteria for patients with varying therapeutic needs resulted in the following four symptom combination groups:

1. Combination 1: chest pain + chest tightness + shortness of breath

2. Combination 2: chest pain + chest tightness + fatigue

3. Combination 3: chest pain + chest tightness + palpitations

4. Combination 4: chest pain + chest tightness + spontaneous perspiration

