### Sample size calculation

Sample size estimation is based on the results of a pilot study that showed the difference in changes in Seattle Angina Questionnaire (SAQ) scores of 2 ± 2.5 between the group receiving QSYQ dripping pills and the group taking TXL capsules. Assuming a two-sided *P*-value of 0.05, 90% power and calculating for a dropout rate of 20%, one would need to have approximately 160 patients with 80 in each treatment group. We used the PAST software program to calculate these statistics (http://folk.uio.no/ohammer/past/) [10]. Therefore, we plan to recruit 40 patients for each of the four symptom combinations, from among whom 20 will be assigned to treatment arm A (QSYQ) and 20 to treatment arm B (TXL). In all, 160 patients will be recruited.

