#### *Comparison of the curative effects of treatment A and treatment B on symptoms related to angina*

Table 1 shows how the intervention treatments work for patients presenting with each of the four symptom combinations.

**Table 1 T1:** Efficacy assessment by category of single symptom combination

**Type of symptom combination**	**Four groups of patients categorized using the efficacy assessment tool**			
	**Group 1**	**Group 2**	**Group 3**	**Group 4**
Combination 1	AB1/*N*	A1/*N*	B1/*N*	ab1/*N*
Combination 2	AB2/*N*	A2/*N*	B2/*N*	ab2/*N*
Combination 3	AB3/*N*	A3/*N*	B3/*N*	ab3/*N*
Combination 4	AB4/*N*	A4/*N*	B4/*N*	ab4/*N*

AB1 to AB4 refer to the number of patients requiring treatment for symptom combinations 1 to 4 and for whom both QSYQ and TXL are effective. A1 to A4 refer to the number of patients requiring treatment for symptom combinations 1 to 4 and for whom QSYQ is effective and TXL is ineffective. B1 to B4 refer to the number of patients requiring treatment for symptom combinations 1 to 4 and for whom QSYQ is ineffective and TXL is effective. ab1 to ab4 refer to the number of patients requiring treatment for symptom combinations 1 to 4 and for whom both QSYQ and TXL are ineffective *N* refers to the total number of patients who fall within each symptom combination group, which is planned to be 40.

Table 2 shows how the intervention treatments will work for patients presenting with two or more of the four symptom combinations. All possible symptom combinations are presented in the table. The total number of patients acting as the denominator increases with the number of symptom combinations involved.

**Table 2 T2:** Efficacy assessment by category of multiple symptom combinations

**Multiple symptom combinations**	**Four groups of patients categorized using the efficacy assessment tool**			
	**Group 1**	**Group 2**	**Group 3**	**Group 4**
Combination (1 + 2)	(AB1 + AB2)/2 *N*	(A1 + A2)/2 *N*	(B1 + B2)/2 *N*	(ab1 + ab2)/2 *N*
Combination (1 + 3)	(AB1 + AB3)/2 *N*	(A1 + A3)/2 *N*	(B1 + B3)/2 *N*	(ab1 + ab3)/2 *N*
Combination (1 + 4)	(AB1 + AB4)/2 *N*	(A1 + A4)/2 *N*	(B1 + B4)/2 *N*	(ab1 + ab4)/2 *N*
Combination (2 + 3)	(AB2 + AB3)/2 *N*	(A2 + A3)/2 *N*	(B2 + B3)/2 *N*	(ab2 + ab3)/2 *N*
Combination (2 + 4)	(AB2 + AB4)/2 *N*	(A2 + A4)/2 *N*	(B2 + B4)/2 *N*	(ab2 + ab4)/2 *N*
Combination (3 + 4)	(AB3 + AB4)/2 *N*	(A3 + A4)/2 *N*	(B3 + B4)/2 *N*	(ab3 + ab4)/2 *N*

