### Strengths and limitations

#### *Strengths*

The following are the potential strengths of our study protocol:

1. Evaluation and interpretation of the therapeutic effects of Chinese patent medicine from the patient’s own perspective

2. Highlighting of individualized evaluation of Chinese patent medicine.

3. Analysis of the curative effects of Chinese patent medicine on single- or multiple-symptom combinations

4. Visualized display of the correspondence between the drug’s efficacy and a specific indication or group of indications

5. Comparison of the therapeutic effects of Chinese patent drugs with other drugs used for similar clinical

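### Table 2 pools patients who each chose a single symptom combination but is labelled as multi-combination patients; it adds nothing to Table 1, and one cell has the wrong denominator

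*Protocol article*

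**What the plan says.** Under Objectives, participants "will first be allowed to choose from among four prespecified groups of symptoms which they would most like to be addressed". Under Patient grouping and treatment allocation, the choice becomes a stratification step before randomization: "we will first categorize eligible participants into four groups on the basis of their varied choice of secondary symptoms to be addressed". The Sample size calculation section sets the numbers: "we plan to recruit 40 patients for each of the four symptom combinations", and "In all, 160 patients will be recruited".

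Table 1 cross-classifies these four groups by four outcomes (both drugs effective, only QSYQ, only TXL, neither). Its footnote says that N "refers to the total number of patients who fall within each symptom combination group, which is planned to be 40".

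The same section then introduces the second table: "Table 2 shows how the intervention treatments will work for patients presenting with two or more of the four symptom combinations". Its 11 rows cover all pairs, triples and the quadruple. Each cell is a sum of Table 1 counts over a multiple of N, and the text says that the denominator grows with the number of combinations in the row.

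The Correspondence analysis section applies the method to both tables. It reads the nearest pair of symptom and outcome points as the strongest relation and takes each drug's characteristic indications from it. The Strengths section lists "Analysis of the curative effects of Chinese patent medicine on single- or multiple-symptom combinations".

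**The concern.** The label of Table 2 promises evidence on patients who need several symptom combinations treated. The counts that fill it are indexed only by the one group each patient chose. A patient may well have several secondary symptoms, since the diagnostic criteria require at least one, but nothing in Table 2 identifies such patients.

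At stake is the trial's main output, the list of indications for which each drug works best. A point for row (1 + 2) lying near the outcome for QSYQ alone would be read as an indication for patients with both symptom sets, when it shows only the average of two groups of different patients. The misprinted denominator, if carried into the software, would also move one row towards the outcome in which neither drug works.

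**Working it through.** **Inputs.** Four groups by chosen symptom (Patient grouping and treatment allocation); 40 per group and 160 in all (Sample size calculation); N planned as 40 (Table 1 footnote); cell formulas and the denominator rule (Table 2 and the text above it).

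**1. The groups do not overlap.** 4 x 40 = 160, which reproduces the stated total. If patients could count in two groups, four groups of 40 would need fewer than 160 people.

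**2. Each Table 2 row is an average of Table 1 rows.** For row (1 + 2), Group 1:

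(AB1 + AB2)/2N = ½ (AB1/N + AB2/N).

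The same holds for every row of k combinations with denominator kN. No cell contains a count that is not already in Table 1.

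**3. Overlap of the rows.**
- Number of rows: 6 pairs + 4 triples + 1 quadruple = 11.
- Rows containing a given combination: 3 pairs + 3 triples + 1 quadruple = 7.
- Weight of one patient across the table, in units of 1/N: 3/2 + 3/3 + 1/4 = 2.75.

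Each group's share of the average row profile is therefore 2.75/11 = 1/4. That average is exactly row (1 + 2 + 3 + 4). With correct denominators, this row lies at the origin of the plot whatever the trial finds, so its position is fixed by construction.

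**4. Denominators.** The kN rule was compared with all 44 printed cells (11 rows x 4 groups), and 43 agree. The exception is row (1 + 2 + 4), Group 4, where ab1 + ab2 + ab4 is divided by 2N = 80. The other three cells of that row are divided by 3N = 120.

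**5. Effect of the cell if used as printed.** Let q be the true Group 4 share in that row. The documents give no value, so a range is assumed.
- Printed cell = 1.5q.
- Row sum = (1 − q) + 1.5q = 1 + 0.5q.
- Group 4 share after the correspondence analysis rescales the row to a profile = 1.5q/(1 + 0.5q).

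| q | printed cell | row sum | profile share |
|---|---|---|---|
| 10% | 15% | 105% | 14.3% |
| 25% | 37.5% | 112.5% | 33.3% |
| 30% | 45% | 115% | 39.1% |
| 50% | 75% | 125% | 60% |

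At q = 25%, 30 of 120 patients are entered as 30/80 = 37.5%, and the profile share is 37.5/112.5 = 33.3%. With 3N, all 11 rows sum to 100%.

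**The case against.** The best defence is that the study calls itself exploratory, that Table 2 is a descriptive display, and that Table 1, which holds all the information, is unaffected by either problem. The 2N is plainly recoverable from the rest of its row and from the stated rule. This stands as a limit on severity. It does not rescue the label, because the article itself sends Table 2 into the analysis that names indications and claims the multiple-symptom analysis as a strength.

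A reader might infer more than the article supports in four ways:

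- **Sevenfold counting.** Seven row appearances might suggest that 160 patients are analysed as 1,120 (6 x 80 + 4 x 120 + 160). The cells are proportions, the weight per patient is 2.75/N, and no test or interval is planned on the table. No standard error or P-value is inflated. The fault is redundancy and overlap.
- **Dropout.** With 20% dropout, rows divided by 40 might be thought to sum to 80%. N is defined as the patients in each group, with 40 only its planned value; how unclassified patients are handled can be left to a fuller document. An equal loss in every group would in any case cancel in the row profiles.
- **Size of the misprint in the plot.** The factor of 1.5 applies to the cell. After rescaling, 25% becomes 33.3%, a factor of 1.33, and only if the misprint is entered literally.
- **A ready substitute.** It is tempting to say that symptoms actually present are already on record. The diagnostic criteria require at least one secondary symptom; the article does not say that all four are recorded for each patient.

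**Conclusion.** The concern holds on the printed text. Table 2 is mislabelled: it pools disjoint single-choice groups and does not describe patients with two or more combinations. With correct denominators and equal N it is an averaging of Table 1, each group being reused in 7 of 11 overlapping rows, and it adds no information. It therefore cannot support multiple-symptom indications or the corresponding claimed strength. These conclusions rest only on the allocation rule, 4 x 40 = 160 and the printed cell formulas.

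The denominator of the Group 4 cell in row (1 + 2 + 4) is wrong and should be 3N. It is probably typographical. Its effect on the plot is conditional on literal use and depends on the unknown true share, for example 25% becoming 33.3%.

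The single-combination analysis from Table 1 is not called into question by this point.

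**What to change.** - Relabel Table 2 and its introductory sentence as pooled single-choice groups.
- Remove Table 2 from the correspondence analysis, or project its rows only as supplementary points on the Table 1 solution, so that they do not shape the axes.
- State that no multiple-symptom indication will be drawn from it, and reword the matching item under Strengths.
- Correct the Group 4 cell of row (1 + 2 + 4) to 3N.

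If the individual secondary symptoms are recorded at screening, a separate descriptive tabulation by symptoms actually present could address the multiple-symptom question. It would group patients differently from the stratification, and its cell sizes would not be controlled.

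The first four changes are edits to text and one formula. They need no new data and no change to recruitment, randomization or treatment. The optional tabulation costs little if the symptoms are recorded; otherwise it would require collecting them.

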### Correspondence analysis

Correspondence analysis (CA) is a statistical technique designed to demonstrate or summarize a set of data in two-dimensional graphical form, typically a biplot, which can help in the detection of the structural relationships among the variables contained in the rows and columns of a contingency table. In this study, SPSS version 16.0 software (SPSS Inc, Chicago, IL, USA) will be used to perform CA of the data in Tables 1 and 2. Statistical analysis will follow the steps listed below:

1. Specify the value of dimensions.

2. For both tables, the number of dimensions will be set at two.

3. Production of a CA plot.

The biplot is a matrix of joint plots of the row and column points. In the biplot, types of symptom combinations and different outcome groups are shown as points. The abscissa value is determined by the score of the first dimension of symptom combinations and outcome groups. The ordinate value is the score of the second dimension of symptom combinations and outcome groups.

4. Calculation of “D (A–B)” refers to the relative distance between point A and point B in the biplot. “a1” and “b1” refer to the abscissa values of point A and point B. “a2” and “b2” refer to the ordinate values of point A and point B.

5. The relative distance between points displayed in the CA plot will be summarized in a table. As prespecified, the pair of symptom combinations and outcome types with the nearest relative distance will signify the most significant correlation. The characteristic indications for which the patent drug is most effective will be found upon careful screening.

6. The value of relative distance between two points in the biplot will be calculated using the following formula.

$$D\left(A‒B\right)=\sqrt{{\left(a1\;‒\;b1\right)}^{2}+{\left(a2-b2\right)}^{2}}$$

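### The trial is sized on a between-drug difference in SAQ change, but no planned efficacy analysis estimates or tests a difference between the drugs

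*Protocol article*

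**What the plan says.** **Sizing.** The Sample size calculation section uses "the difference in changes in Seattle Angina Questionnaire (SAQ) scores of 2 ± 2.5" between the QSYQ and TXL groups. It adds "Assuming a two-sided *P*-value of 0.05" and "90% power and calculating for a dropout rate of 20" percent, and arrives at "approximately 160 patients with 80 in each treatment group", that is 40 per symptom combination (20 per sequence).

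**Aim.** The Objectives section intends to characterise each drug "By analyzing and comparing the effects of the two drugs for each symptom group".

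**Efficacy analysis.** Under Efficacy assessment tools, each patient's SAQ score in each period is compared with an MCID specific to that treatment and period, and labelled effective or ineffective. The A-then-B and B-then-A patients are merged into four groups: both drugs effective, A only, B only, neither. Tables 1 and 2 give the share in each group per symptom combination, and SPSS "will be used to perform CA of the data in Tables 1 and 2". The combination and outcome group lying closest in the two-dimensional plot are taken as most strongly related.

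**Tests named elsewhere.** The t-test, analysis of variance and chi-square test are assigned to baseline balance, and a chi-square test to adverse events. None is assigned to SAQ.

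**The concern.** A power statement is a statement about one particular test of one particular quantity. Here the quantity is a difference in mean SAQ change between two drugs, and the analysis section has no place where that quantity, or any A-minus-B contrast, is computed. A reader of the results could not say by how much one drug was better, overall or within a symptom group, nor how uncertain that is.

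Two further features sharpen this. Correspondence analysis is descriptive: some pair of points is always nearest, whatever the data, and no interval accompanies the distance. Reducing a score to effective or ineffective also loses information, which matters most at 40 patients per combination, where the drugs are to be compared.

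**Working it through.** **1. The plan's own figure.** Inputs from the Sample size calculation section: difference 2, SD 2.5, two-sided 0.05, 90% power, 20% dropout. For two parallel means:

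n per arm = 2 × (1.960 + 1.282)² × 2.5² / 2² = 32.8, so 33 per arm and 66 in total. With dropout, 33 / 0.8 = 41.25, so 42 per arm and 84 in total.

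The stated 160 is not reproduced. It appears if the SD is 2.5 × √2 = 3.54 (65.7, so 66 per arm) and dropout is added as 66 × 1.2 = 79.2, so 80 per arm. That is a separate matter. What counts here is that every version is a comparison of two means.

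**2. Match between sizing and analysis.**

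| | Sample size section | Efficacy analysis |
|---|---|---|
| Quantity | difference in mean SAQ change | shares in four outcome groups |
| Scale | continuous | effective / ineffective |
| Inference | two-sided 0.05, 90% power | nearest biplot distance, no test or interval |
| Period term | not applicable | none |

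**3. What the plot can show.** Correspondence analysis works on departures of each row from the average row: inertia = Σ (p_ij − r_i c_j)² / (r_i c_j). If all four combinations have the same expected shares, for example because one drug is better by the same amount in each and response is otherwise alike, then p_ij = r_i c_j in every cell and inertia is 0. A uniform difference would be visible in the raw shares of Table 1, but not in the distances from which conclusions are drawn. Those would reflect sampling noise.

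**4. Illustration of the cost of the cut, per combination.** From the documents: 40 patients, 20% dropout, so 40 × 0.8 = 32 completers; difference 2; SD 2.5. Assumed: 2.5 is the SD within each period (the text does not say); scores are normal; within-patient correlation ρ is 0, 0.3 or 0.5; the cut-off is near the centre (1.6 or 2.0 with means of 3 and 1); Groups 2 and 3 are filled according to their titles. Because correspondence analysis makes no test, an exact test on A-only versus B-only patients is used as a stand-in.

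- Paired analysis: SD of the difference = 2.5 × √(2(1 − ρ)); noncentrality = 2 × √32 / SD of the difference.
- Cut analysis: A-only and B-only probabilities from the bivariate normal (shown for cut-off 2.0), then the exact binomial test on discordant patients.

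| ρ | SD of difference | Noncentrality | Paired power | A-only / B-only | Exact-test power |
|---|---|---|---|---|---|
| 0 | 3.54 | 3.20 | 87% | 43% / 12% | 61–62% |
| 0.3 | 2.96 | 3.82 | 96% | 39% / 8% | 69–70% |
| 0.5 | 2.50 | 4.53 | 99% | 36% / 5% | 76–77% |

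For a true difference of 1 point the paired analysis has about 34–59% and the counts about 17–22%.

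**5. Sensitivity.** With the cut-off 1 SD above the centre, the exact test falls to about 40–48% for 2 points. The less conservative mid-p version gives 70–83% with a central cut. At ρ = 0.7 with a central cut the comparison is 100% against 86% (exact) or 91% (mid-p). The gap narrows at high correlation and widens as the cut moves off centre.

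**The case against.** - **The study is exploratory and tests a method.** The Discussion says so, and the MCID-plus-plot approach is what is being tried out. This stands as a reason to keep that approach in place. It does not explain a power statement that refers to a different analysis.
- **A fuller analysis plan may compare mean SAQ.** Possible, but the article sets out its efficacy steps one by one, with a decision rule, and this is not among them.
- **The pairing is used.** True: each patient is classified jointly on both drugs, so a within-patient comparison exists, in coarse binary form. It would be wrong to say the crossover is ignored.
- **The 90% is claimed for 80 against 80, not per combination.** Also true. With all 128 completers pooled and groups correctly labelled, even the binary comparison has about 100% power in the setting tried (ρ = 0.5, central cut). The loss concerns the symptom groups, and the illustration contradicts no stated per-group power.
- **Period effects.** A reader might infer that merging sequences without a period term biases the drug comparison. It does not, if groups follow their titles. With identical drugs, ρ = 0.5 and a 1-point shift between periods, first-only and second-only shares go from 16.6% and 16.4% to 9.2% and 24.0%. With "randomly assign them to one of the two treatment arms at a ratio of 1:1", each pooled drug cell is (9.2 + 24.0)/2 = 16.6%, against (16.6 + 16.4)/2 = 16.5% without a shift. Only individual labels are affected.
- **Size of the information loss.** A reader might infer that the cut throws away most of the information. For a central cut, the numbers needed for 90% power (continuous against binary, mid-p) are 36 and 56, 26 and 46, 20 and 38 at ρ = 0, 0.3 and 0.5. The loss is 1 − 36/56 = 36%, 1 − 26/46 = 43% and 1 − 20/38 = 47%: substantial, but under half.

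**Conclusion.** The point holds as a mismatch. The trial is sized on a mean difference between drugs, and the stated efficacy analysis yields no estimate, interval or test of any such difference, overall or by symptom group. That conclusion comes from the text and needs no assumption.

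The power figures (about 87–99% against 61–77% per combination for 2 points) are illustrative. They rest on an assumed cut-off, correlation and reading of the SD, and on a test the protocol does not contain. They also assume the outcome groups follow their titles. Items 5.b.ii and 5.c.ii, as printed, reverse the titles of Groups 2 and 3 for B-then-A patients; applied literally, the drug contrast between those groups cancels. Those items must be reconciled with their titles whichever analysis is used.

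**What to change.** Add, as the analysis that matches the sample size, a linear mixed model of continuous SAQ with treatment, period, symptom combination, treatment-by-combination interaction and a patient effect (or the equivalent paired crossover analysis). Report A minus B with a 95% CI overall and for each combination. Use end-of-period SAQ, which the protocol already collects after both treatment periods. Adjust for pre-treatment SAQ only if it is collected, since the data-capture section names no such measurement. Restate the power for this analysis, saying whether 2.5 is the SD per period or of the within-patient difference.

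Keep the four-group tables and the correspondence analysis as the exploratory method under test, and say that biplot distances are descriptive.

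The cost is a paragraph of analysis text and slight extra analysis work, with no new data. Adding pre-treatment SAQ would mean extra data collection and is optional.

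### Drug-specific indications are read from nearest distances in the correspondence plot, with no test that the QSYQ-versus-TXL contrast differs between symptom combinations

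*Protocol article*

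**What the plan says.** Under Objectives, the protocol article sets out what the comparison is for: "By analyzing and comparing the effects of the two drugs for each symptom group", the investigators intend to "identify the best targeted indications for each drug".

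The route to that conclusion is fixed in two places. Tables 1 and 2 count patients by symptom combination (four rows of a planned 40) and by outcome group: both drugs effective (Group 1), only QSYQ (Group 2), only TXL (Group 3), neither (Group 4). The section Correspondence analysis then plots both tables: "For both tables, the number of dimensions will be set at two". Step 5 gives the decision rule, "As prespecified, the pair of symptom combinations and outcome types with the nearest relative distance will signify the most significant correlation", and the conclusion drawn from it, "The characteristic indications for which the patent drug is most effective will be found upon careful screening".

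The only significance tests named are for baseline balance and for adverse events. The sample size rests on one overall two-group difference in SAQ change, not on a difference between symptom combinations.

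**The concern.** Saying that QSYQ suits one symptom combination and TXL another is a claim of interaction: the drug contrast must differ between combinations. The rule never examines that. It ranks distances and reads the smallest as significant, although a smallest distance exists in any table, including one produced by chance alone. The rule also has no minimum distance, confidence region or overall test that could lead to the answer that no combination stands out.

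Better distances would not cure this. With sound estimates in every row, a drug that looks better in one row and not in another has still not been shown to act differently in the two. Table 2 adds no independent evidence, because its rows only pool those of Table 1.

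At stake is the trial's main product. A chance pattern could be published as the characteristic indication of a marketed drug, and the evaluation method could appear to have worked when there was nothing to find.

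**Working it through.** **The plan's own figure.** The stated input is a "difference in changes in Seattle Angina Questionnaire (SAQ) scores of 2 ± 2.5", two-sided 0.05, 90% power and 20% dropout. Per arm, n = 2(1.96 + 1.2816)² × 2.5² / 2² = 2 × 10.51 × 6.25 / 4 = 32.8, so 33. Then 33 / 0.8 = 41.25, so 42 per arm and 84 in total, against the stated 80 and 160. The figure is not reproduced on this direct reading. That is a separate matter and nothing below depends on it.

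**Inputs to the check.** From the document: four combinations ("we plan to recruit 40 patients for each of the four symptom combinations"), hence 40 × 0.8 = 32 completers per row; two dimensions; Euclidean distance. Assumed, because the document gives none: the outcome rates. Also assumed: the screening step assigns to Group 2 and to Group 3 the combination nearest to each.

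**Behaviour with no drug-by-symptom difference.** Four rows were drawn from the same multinomial distribution, with 40 or 32 patients per row and 3,000 trials per setting. The last column requires a 3-df chi-square on Group 2 versus Group 3 counts by combination to give P < 0.05 first.

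| Rates in Groups 1/2/3/4 (%) | Drugs matched to different combinations | Same, after requiring the test |
|---|---|---|
| 25/25/25/25 | 90–91% | 4–5% |
| 40/20/20/20 | 88–89% | 5% |
| 50/15/15/20 | 84–85% | 4–6% |
| 40/30/10/20 (QSYQ uniformly better) | 88% | 5% |
| 60/10/10/20 and 30/10/10/50 | 80–83% | 4–5% |

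Symmetric and principal normalisation gave nearly the same results. For scale, two independent random picks from four combinations differ with probability 1 − 1/4 = 75%.

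**Behaviour with real heterogeneity.** The base is 40/20/20/20. One combination is shifted to 30/10 in Groups 2/3 and another to 10/30. The two drugs are then matched to different combinations in 98–99% of trials, so the output looks much the same as under no interaction.

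**Power of the count-based test, with Groups 2 and 3 correctly labelled.** For the 30/10 and 10/30 shift: 55% at 32 per row and 67% at 40. For 35/5 and 5/35: 95% and 98%.

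**The same test with the labels as written.** Under Efficacy assessment tools, item 5.b.ii covers patients given B first. It requires the first score to exceed MCID2 (B effective) and the second to fall below MCID3 (A ineffective), yet it sits under the heading for A effective and B ineffective. Item 5.c.ii is reversed in the same way. With 1:1 allocation to sequence, a 30/10 row becomes (30 + 10)/2 = 20 in each group and the drug contrast cancels. With 16 patients per sequence per row, power falls from 55% to about 4%, and from 95% to about 3%.

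**Power of a model-based test.** Take a 3-df F test on within-patient SAQ differences, with a 2-point drug difference in one combination and none in the other three. The non-centrality is n × 2² × (3/4) / SD² = 3n / SD². If the SD of the within-patient difference is 2.5 and n = 32, this is 96 / 6.25 = 15.4, and power is about 91%. If that SD is 2.5√2 = 3.54, it is 96 / 12.5 = 7.7, and power is about 62%. Both SDs are assumptions.

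**The case against.** Four points on the other side deserve weight.

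- **The written rule names a single nearest pair.** It does not say that each drug-only group receives its own nearest combination. On the single-pair reading, under a 40/20/20/20 null, that pair involves Group 1 or Group 4 in about half of trials, and in about 75% at 60/10/10/20. Neither group distinguishes the drugs. A reader might infer that the plan always gives each drug a different indication, or that it cannot come out negative. The document does not support that.
- **The 80–91% is not a false-positive rate** to set against 5%. Choosing among four combinations accounts for 75% by itself. The figure shows only that separation of the two drugs on the plot is not evidence of interaction.
- **The study calls itself exploratory,** and it lists the method's practicality as still to be tested. This lowers the consequence but does not remove it, because the Objectives and step 5 still present the result as indications of each drug.
- **Interaction tests are often left to an analysis plan that is not shown.** That would answer a complaint of mere omission. Here the article fixes the rule, calls it prespecified and equates nearness with significance, so the fault lies in what is stated.

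**Conclusion.** The point holds in this form: the plan infers drug-specific indications from nearest distances without testing whether the drug contrast differs between combinations, so chance patterns can be reported as indications. The 80–91% rests on assumed outcome rates and on one reading of the screening step. It is an illustration, not a property of the plan under every reading. That a nearest pair always exists, and that no heterogeneity test precedes the claim, needs no such assumption. The change should be made before analysis. It does not call the design or the data collection into question.

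**What to change.** Prespecify one drug-by-symptom-combination test as the precondition for any symptom-specific claim. The preferred form is the drug × combination term (3 df) in a within-patient crossover model of SAQ with period and sequence, because it does not use the outcome groups.

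The alternative is to compare Group 2 with Group 3 counts across the four combinations (3 df, exact if sparse). It may be used only after items 5.b.ii and 5.c.ii have been reconciled with their headings. An overall chi-square on the 4 × 4 table is no substitute, since it also reacts when symptom groups differ in their response to both drugs alike.

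If the test does not support heterogeneity, report the overall QSYQ-versus-TXL comparison, state that no symptom-specific indication was shown, and keep the correspondence plot as description. Step 5 should no longer equate the nearest distance with significance.

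The cost is about a paragraph of analysis wording and no new data; the count-based option also needs the group definitions corrected. The real price is limited power for moderate heterogeneity, so the trial may have to report that no distinct indication was shown.
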